## Methods

This is a pilot randomised control parallel group trial of three strategies to improve patient recall in the self-report of health status using quality of life questionnaires. These strategies to aid patient recall will be tested in a single centre, randomised controlled trial comparing alternative strategies of assessing change in patient reported outcomes with treatment in an acute care hospital in Australia. The parallel groups comprise COPD patients commencing pulmonary rehabilitation and COPD patients waiting to commence the program. We will compare three strategies to improve patient recall with the standard approach of patient’s completing the questionnaires at each study time point. These new strategies in addition to current practice are (1) the use of tablet technology’s audio-visual functionality and (2) the provision of patient access to their baseline questionnaire responses prior to completion of questionnaires at follow-up. Additionally, we are assessing the feasibility of using these patient strategies to improve patient recall when completing self-report PROs questionnaires in a busy acute care hospital. Feasibility will be assessed according to the National Institute for Health Research (NIHR) feasibility study criteria (Table 1) [18].

**Table 1 Tab1:** Feasibility assessment for recall study

Feasibility item	Record
Willingness of clinicians to refer patients to the study	Number of referrals to study
Willingness of participants to be involved in the study	Number of patients approached but chose not to participate
Number of eligible patients	Number of patient who are eligible based on criteria
Number of participants that dropped out of study	Number of participants who withdrew and reasons or died
Follow-up rates	Number of participants who completed time 2 questionnaires
Length of time to complete recruitment of participants	Time in months
Length of time to administer intervention	Time in minutes
Length of time to analyse data	Time in days

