#### Participant timeline

COPD patients attending the respiratory service of a large tertiary hospital who are commencing or waiting to commence pulmonary rehabilitation will be invited to consider taking part in the patient recall study. Pulmonary rehabilitation staff receive the patient referrals from the hospital’s medical and nursing staff. The pulmonary rehabilitation clinical staff will initially approach potential participants, and if the patient verbally consents, the research assistant will further assess the patient for eligibility and their willingness to participate in the study. Patients will be given the study’s approved patient information sheet to read prior to being asked if they will continue with the consenting and enrolment process with the research assistant. All engagement and communication with participants will be conducted in a separate private office away from the clinical area. Once the patient is consented and enrolled, the research assistant will assign the participant to an arm of the study using the randomisation code. Baseline data will be collected and the randomised intervention will commence. At the second and final data collection point, the intervention will be implemented and follow-up data collected. Once 30 participants are enrolled and their data collected at baseline and follow-up appointments, the study’s data collection will end.

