#### Sample size

For this pilot randomised control trial and feasibility study, we did not generate a sample size. Thirty (30) adults with COPD, who are either commencing or wait-listed for pulmonary rehabilitation, will be enrolled in this study. The data generated from this study will be used to estimate important parameters that are required to design a larger randomised controlled study to evaluate the role audio-visual recordings using tablet computer technology may play in assisting patient’s recall of their previous health state.

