#### Recruitment

Our pulmonary rehabilitation service is the largest in the health district, which is located on the hospital campus. COPD patients referred to pulmonary rehabilitation can wait up to 6 weeks before commencing the program. All COPD patients, with a referral to or attending the pulmonary rehabilitation program, will be informed about the study and invited to consider participating.

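### Clinician willingness to refer is recorded as a bare referral count while enrolment stops at 30; without the number of candidates, low willingness cannot be told from low caseload

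*Protocol article*

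**What the plan says.** Table 1 (Methods) lists eight feasibility items, each with what is to be recorded. For clinicians' readiness to refer, the item and its record read "Willingness of clinicians to refer patients to the study Number of referrals to study", with no denominator and no unit of time. The list under Data collection methods repeats the item and adds neither.

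The stopping rule is under Participant timeline: "Once 30 participants are enrolled and their data collected at baseline and follow-up appointments, the study’s data collection will end". The figure of 30 is set by choice; under Sample size the authors write "we did not generate a sample size".

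Three other rows of Table 1 bear on the point:
- refusals: "Number of patients approached but chose not to participate"
- eligibility: "Number of patient who are eligible based on criteria"
- duration, in months: "Length of time to complete recruitment of participants"

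Recruitment describes who is to be reached: "All COPD patients, with a referral to or attending the pulmonary rehabilitation program, will be informed about the study and invited to consider participating". Participant timeline gives the order of events. Hospital staff refer patients into rehabilitation, rehabilitation staff make the first approach about the study, and the research assistant sees only those who agree verbally. Statistical methods says that feasibility will be reported descriptively and names rates among the statistics, without assigning a denominator to any item.

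**The concern.** A count measures willingness only if the opportunity to refer is fixed or known. Here the number enrolled is fixed instead. Referrals continue until 30 people are in, so reluctant clinicians lengthen the calendar time rather than lower the count. The count does respond to something else: the fewer patients who are eligible or consent, the more referrals are needed, and the more willing the clinicians appear.

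Ability to recruit is part of the feasibility outcome, and Sample size says that the pilot's data will inform the design of a larger trial. If recruitment is slow, the designers need to know whether staff passed on few of the patients they had or whether few patients came through the service. The first calls for work with clinicians; the second calls for more sites or more time.

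**Working it through.** **Inputs.** From the protocol article: enrolment target 30, willingness recorded as a count, months recorded separately. Not in the document, so assumed: eligibility e (0.5 to 0.9), consent c (0.4 to 0.8), candidates per month N (20), and the share of candidates whom clinicians pass on, w (0.1 to 0.9). The plan derives no figure that could be reproduced.

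**Step 1: expected count.** Each referral leads to an enrolment with probability e × c, and referrals run until 30 are enrolled (negative binomial sampling).

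- Mean = 30 / (e × c)
- SD = √(30 × (1 − e × c)) / (e × c)

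At e = 0.7 and c = 0.6, e × c = 0.42. The mean is 30 / 0.42 = 71.4, the SD is √(30 × 0.58) / 0.42 = 9.9, and the 95% range is 54 to 93. Over the assumed ranges the mean runs from 30 / 0.72 = 41.7 (95% range 35 to 50) to 30 / 0.20 = 150 (106 to 202). The share w appears in neither formula.

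**Step 2: vary willingness.** Simulation with 20,000 runs, e = 0.7, c = 0.6, N = 20:

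| w | Mean referrals | Months | Referrals per month | Referrals per candidate |
|---|---|---|---|---|
| 0.9 | 71.2 | 4.0 | 18.0 | 0.90 |
| 0.6 | 71.4 | 6.0 | 12.1 | 0.60 |
| 0.3 | 71.4 | 11.9 | 6.1 | 0.30 |
| 0.1 | 71.3 | 35.7 | 2.0 | 0.10 |

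The count does not move. The monthly rate and the proportion both follow w.

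**Step 3: what the count does follow.** With e = 0.8, consent of 0.5 gives 30 / 0.40 = 75 referrals and consent of 0.8 gives 30 / 0.64 = 46.9. The ratio is 75 / 46.9 = 1.6, so lower patient consent raises the item by 60%.

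**Step 4: what the other rows recover.** At e = 0.7 and c = 0.6, 71.4 × 0.7 = 50 of those referred are eligible, of whom 20 decline and 30 enrol. If refusals are counted among eligible patients, 30 / (30 + 20) = 0.6 returns the consent rate. Patient refusal can therefore be estimated from planned data.

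**Step 5: what stays confounded.** Referrals per month = w × N. Six a month fits w = 0.30 with N = 20 (0.30 × 20 = 6) and equally w = 0.90 with N = 6.7 (0.90 × 6.7 = 6). Only a record of N separates the two.

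**Step 6: selective referral.** If reluctant clinicians send only promising candidates, so that e and c rise from 0.7 and 0.6 to 0.9 and 0.8, the expected count falls from 71.4 to 41.7. The count then changes, but because of who was chosen; it still does not show the share passed on.

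**The case against.** The strongest reply is that Table 1 lists raw data to capture, not the statistic to be interpreted. The follow-up rate is likewise recorded by its numerator alone, Statistical methods provides for rates, and a journal article may leave the conversion to a fuller document. This has weight, and nothing in the article says that the bare count will be the final judgement. But the two rows differ. For follow-up, the denominator is the 30 enrolled; for referral, the denominator must be collected prospectively, and no listed item clearly collects it.

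A second reply is that the eligibility row may already supply the denominator. It would if it covered all candidates. The row does not say so, and Participant timeline has the research assistant assess eligibility after the patient has agreed to be seen, which points towards those referred only. The text leaves this open.

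A third reply is that everyone is to be invited, so willingness is not in question. That states an intention. A proportion would show whether it was met; a count cannot.

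A reader might also infer two stronger claims. One is that the pilot cannot tell clinicians not referring from patients declining. The documents do not support this: refusals, eligible patients and months are all recorded, and at a stable caseload referrals per month separates willing from reluctant clinicians. The other is that the count is identical whatever clinicians do. It is the same only in expectation, with an SD of about 10 in the central case, and only if referral is not selective.

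**Conclusion.** The point holds in a limited form. With enrolment stopped at 30, the recorded referral count carries no information in expectation about the share of candidates passed on: about 71 referrals at 90% or at 10%, under eligibility 0.7, consent 0.6 and non-selective referral. Those rates are assumptions. Other values move the expected count between about 42 and 150 but do not bring willingness into it. The article does not say whether drop-outs are replaced; replacement would shift the target slightly and leave the argument unchanged.

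What the planned data cannot resolve is low willingness against low caseload, because the number of candidates is not clearly recorded. Severity is minor: this is one of eight descriptive items, and the article attaches no threshold or go/no-go rule to it.

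**What to change.** In Table 1 and in the list under Data collection methods, replace the bare count with a proportion:

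- **Numerator:** COPD patients whom rehabilitation staff approach about the study, counted before the patient's verbal consent. Counting those who reach the research assistant would bring patient refusal back into the measure.
- **Denominator:** all COPD patients referred to or attending pulmonary rehabilitation during the recruitment period, taken as an anonymous monthly tally from the service list.

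Report the proportion with a 95% confidence interval, alongside referrals per month, and keep patient refusal as a separate item. State whether the eligibility row covers all candidates or only those referred. State also that the clinicians meant are the rehabilitation staff who make the approach, since the article also speaks of hospital staff referring into the programme, and that step would need a different denominator.

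Precision would be usable. With 60% approached and about 71.4 approaches, the denominator is 71.4 / 0.6 = 119, and the approximate half-width is 1.96 × √(0.6 × 0.4 / 119) = 0.09, or about 0.51 to 0.69.

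The cost is a revised line in each of the two lists and a small amount of monthly tallying. No extra visits or participants are needed.

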### Participants, interventions and outcomes

#### Study setting

Participants will be recruited from the COPD patient population who attend a respiratory service at Liverpool Hospital, Sydney, a large tertiary hospital in Australia. The study has been accepted and recorded on the Australian and New Zealand Clinical Trial registry (ANZCTR No. 12618001605280) and lists the single site where this study is being conducted.

#### Eligibility criteria

To be eligible for the study, adults must have a medical diagnosis of COPD and be able to read to year 7 standard to ensure unaided completion of the quality of life questionnaires. Patients with COPD who have significant medical comorbidities that require ongoing acute care will be excluded from participating in the study. Any COPD patient with significant neurological and cognitive impairment such as medically diagnosed dementia will also be excluded. After confirming the patient’s eligibility, study information will be given to patients by the research assistant. Once the patient has had time to review the study information, consent will be sought (Additional file 1). On gaining consent, the patient will be enrolled into an arm of the study and interviewed by the research assistant and data collected. Participants will be re-interviewed 1 month later from the time of their first interview with the research assistant.

#### Interventions

Study participants will be randomly allocated to one of the following strategies to enhance patient recall (Fig.1):Tablet computer technology audio-visual recording: As part of recording participants at baseline, they will be asked to respond to questions on the health questionnaires which they have just completed by self-report. Participants will be shown this video 1 month later prior to the completion of the follow-up questionnaires.Shown hard copy of baseline responses: Participants will be provided with hard copies of their baseline responses to review immediately prior to completing follow-up questionnaires.Standard practice: Participants will be required to complete the health questionnaires at baseline and 1 month later without access to their previous responses or an audio-visual recording and receive no feedback on their baseline responses.

**Fig. 1 Fig1:**
[figure not shown]
Study participant numbers in each group and study interventions protocol

Clinical care will not be affected and the clinical team will continue the medical management of the patient during the timeframe of the study. The investigator team members are not part of the clinical or pulmonary rehabilitation teams. Patients who become clinically unwell and unable to attend the follow-up appointment will be included in the analysis.

#### Outcomes

There are two outcomes associated with this study; evaluating the feasibility of conducting this study in an acute tertiary admission hospital using the National Institutes for Health Research’s feasibility criteria and testing the hypothesis related to the difference in quality of life indices. The feasibility outcome for this study is the ability to recruit participants who are wait-listed or attending the pulmonary rehabilitation program, administer the interventions in a timely manner and the ease of conducting and completing this study in a busy clinical environment without disruption to the pulmonary rehabilitation service or patient care. The secondary outcome of this randomised controlled trial is concerned with the impact of the patient recall strategies on the quality of life questionnaires’ responsiveness. Specifically, we are measuring the magnitude of statistical difference of quality of life between the three arms of the study.

#### Participant timeline

COPD patients attending the respiratory service of a large tertiary hospital who are commencing or waiting to commence pulmonary rehabilitation will be invited to consider taking part in the patient recall study. Pulmonary rehabilitation staff receive the patient referrals from the hospital’s medical and nursing staff. The pulmonary rehabilitation clinical staff will initially approach potential participants, and if the patient verbally consents, the research assistant will further assess the patient for eligibility and their willingness to participate in the study. Patients will be given the study’s approved patient information sheet to read prior to being asked if they will continue with the consenting and enrolment process with the research assistant. All engagement and communication with participants will be conducted in a separate private office away from the clinical area. Once the patient is consented and enrolled, the research assistant will assign the participant to an arm of the study using the randomisation code. Baseline data will be collected and the randomised intervention will commence. At the second and final data collection point, the intervention will be implemented and follow-up data collected. Once 30 participants are enrolled and their data collected at baseline and follow-up appointments, the study’s data collection will end.

#### Sample size

For this pilot randomised control trial and feasibility study, we did not generate a sample size. Thirty (30) adults with COPD, who are either commencing or wait-listed for pulmonary rehabilitation, will be enrolled in this study. The data generated from this study will be used to estimate important parameters that are required to design a larger randomised controlled study to evaluate the role audio-visual recordings using tablet computer technology may play in assisting patient’s recall of their previous health state.

#### Recruitment

Our pulmonary rehabilitation service is the largest in the health district, which is located on the hospital campus. COPD patients referred to pulmonary rehabilitation can wait up to 6 weeks before commencing the program. All COPD patients, with a referral to or attending the pulmonary rehabilitation program, will be informed about the study and invited to consider participating.

### Assignment of interventions

#### Allocation

For this pilot study, participants will be allocated to one of three recall strategies; tablet technology audio-visual recording, reviewing their previous responses or standard practice (Fig. 1).

#### Sequence generation

Eligible participants will be randomised 1:1:1 assigned ratio to one of the three intervention arms in both the pulmonary rehabilitation and wait list groups using the computer-generated randomisation code.

#### Allocation concealment mechanism

The research assistant will hold the allocation code and the study investigators do not have access to the code or the participant assignment information. Clinical staff and the study investigators will be unaware of a participant’s assignment to an intervention arm of the study.

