#### Consent or assent

The research assistant is responsible for consenting potential participants after they have read and indicated they understood the study information to ensure informed consent. Other forms of consent, assent or authorised surrogates, will not be acceptable for enrolment into this patient recall study.

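### The research assistant who screens and consents patients also holds the allocation code, with no described safeguard against foreseeing the next arm, and assignment is placed before baseline data collection

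*Protocol article*

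**What the plan says.** Several sections of the protocol article describe the route into the trial.

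- **Participant timeline.** Clinical staff make the first approach. Then "the research assistant will further assess the patient for eligibility and their willingness to participate in the study".
- **Consent or assent.** "The research assistant is responsible for consenting potential participants".
- **Implementation.** The biostatistician generated the code, and the research assistant uses it to assign the arm.
- **Allocation concealment mechanism.** "The research assistant will hold the allocation code and the study investigators do not have access to the code". Clinical staff and investigators are said not to know who is in which arm. The research assistant is not in that list.
- **Participant timeline, on order.** "Once the patient is consented and enrolled, the research assistant will assign the participant to an arm of the study using the randomisation code". The next sentence reads: "Baseline data will be collected and the randomised intervention will commence".
- **Eligibility criteria, on order.** "On gaining consent, the patient will be enrolled into an arm of the study and interviewed by the research assistant and data collected".
- **Blinding.** Participants and the treating team are described as blind. The research assistant is not mentioned.
- **Statistical methods.** The outcome is each participant's change in questionnaire score over one month. It is contrasted between rehabilitation and wait-list patients, and that contrast is then compared between groups.

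**The concern.** Allocation concealment protects the decision to enrol. Whoever decides whether and when a patient enters should be unable to foresee the next arm. Here the code is withheld from the investigators, who are given no part in enrolment, and from clinical staff, who only make the first approach. It is placed with the person who makes the later decisions. Selective enrolment needs no bad faith: hesitating over a camera-shy patient when the next slot is filming would be enough.

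The order of steps adds a second route. If the arm is fixed before baseline, the baseline answers are collected when at least one party may know it, and those answers are subtracted in the outcome.

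What is at stake is the comparison of the three recall strategies and the parameter estimates that the Sample size section says will be used to design a larger trial. The piloted enrolment procedure might also be carried forward as it stands.

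**Working it through.** The plan states no figure on this point. The Sample size section reports that no calculation was made, and no standard deviation or effect size is given. The check is therefore a trace of who does what, and in which order.

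1. **Who controls entry.** First approach: clinical staff. Eligibility and willingness: research assistant (Participant timeline). Study information: research assistant (Eligibility criteria). Consent: research assistant (Consent or assent). Assignment: research assistant (Participant timeline, Implementation).

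2. **Who is kept from the code or the assignments.** Investigators and clinical staff (Allocation concealment mechanism). Compared with step 1, only the first approach is protected. The eligibility and consent decisions are made by the holder of the code.

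3. **Is there room for judgement at entry?** Yes. The exclusions turn on whether comorbidity and cognitive impairment are significant, there is a reading-level requirement, and willingness is assessed by the research assistant.

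4. **Order as written.** Approach, eligibility, consent, assignment, baseline data, start of intervention, follow-up at one month. The Participant timeline and Eligibility criteria agree that assignment comes before baseline data.

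5. **How a baseline disturbance would reach the result.** For one participant, change = follow-up − baseline. For strategy s, responsiveness is R(s) = mean change in rehabilitation − mean change on the wait list. Suppose knowledge of the arm shifts mean baseline by a in the rehabilitation group and by b in the wait-list group, with follow-up unaffected. Then R(s) moves by (−a) − (−b) = b − a. A shift common to both groups cancels in R(s), and a shift that differs does not. If the three arms are instead compared directly on change, as the Outcomes section can be read, a common shift a = b moves that arm's mean change by −a and does not cancel. The document gives no basis for a value of a or b.

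6. **When the arm is actually needed.** Under Interventions, the recording follows questionnaires that the participant has already completed, the hard copy is shown only at follow-up, and standard practice needs no action. No intervention step requires the arm before the baseline questionnaires are finished.

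**The case against.** The case on the other side is substantial, and much of it limits the point.

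- **The form of the code is not given.** It could be an open list, sealed or held in software, and a condensed article may leave such mechanics to the full protocol. A reader might infer that the next arm is known for all 30 participants. The text does not support that. It shows exposure, not foreknowledge. What stands is that the article fills in its concealment section, names the enroller as holder of the code, and describes no safeguard.
- **Baseline answers are self-completed.** Nothing says that participants learn their arm first, and they are described as blind. That description is hard to sustain once filming begins, but it counts against assuming earlier knowledge. Influence at baseline would be indirect. What stands is the research assistant's possible knowledge and the stated order.
- **Lost baselines.** A reader might infer that someone who refuses filming leaves no baseline. But filming starts after the questionnaires, so a refusal at that moment leaves them in hand. An earlier refusal presupposes that the arm was disclosed, which is not stated.
- **Follow-up.** A reader might also infer that the research assistant runs the follow-up visit. The Eligibility criteria wording ties that role clearly only to the first interview, and the Participant timeline describes follow-up in the passive.
- **Scope for steering is narrowed.** All referred or attending COPD patients are to be invited (Recruitment), and the first approach is by staff unaware of assignments. The later judgements on eligibility and willingness remain.
- **It is a pilot.** Feasibility is the main purpose, and responsiveness is called the secondary outcome. This lowers the severity but does not remove the point, because the data are meant to inform a larger trial.

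**Conclusion.** The point holds as a weakness in a stated arrangement, not as proof that bias will occur. Enrolment and custody of the code rest with one person without a described safeguard, and assignment is written ahead of baseline collection. The secondary responsiveness comparison and the parameters for the larger trial are left open to bias.

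The size cannot be derived from the document. One could assume an even split, 30 / (3 × 2) = 5 per cell, and note that one participant whose change differs by 1 SD moves a cell mean by 1/5 = 0.2 SD. A reader should not take that as an estimate. The 1 SD is arbitrary, the split between groups is not given in the visible text, and the standard error of a mean of five is itself 1/√5 = 0.45 SD.

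The conclusion assumes that the sections mean what they say about who holds the code and about the order of steps. If the full protocol provides sealed or central release, the first limb falls away. If it places baseline before assignment, the second does. Given the pilot status, this should be fixed, but it does not invalidate the study.

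**What to change.** Amend three sections of the protocol: Eligibility criteria, Participant timeline and Allocation concealment mechanism.

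- The biostatistician who generated the sequence, or another person not involved in enrolment, keeps it. The research assistant no longer holds it.
- Each assignment is released by phone or e-mail, or from sequentially numbered, opaque, sealed envelopes, separately for the rehabilitation and wait-list groups.
- The order is fixed as: eligibility, consent, baseline questionnaires and functional tests, release of the assignment, then the recording if allocated.

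The cost is small: a minor amendment, a set of envelopes or a contact for release, and no extra visit. If the numbers in the two groups are not fixed in advance, 30 envelopes are not enough and each group's sequence needs spares. The article does not say where the functional tests fall relative to the recording, so the recording may have to move to after them. The change prevents foreknowledge and keeps the baseline independent of the arm. It does not blind the research assistant after release, and the text should not claim that it does.
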